## Background

Cervical cancer (CC) most frequently arises from persistent infection with oncogenic high risk (HR-) human papillomavirus (HPV) types [1]. Due to global disparities in access to health care services and concurrent epidemiological risk factors (e.g., HIV infection), CC remains a major cause of morbidity and premature mortality in many low- and middle-income countries (LMICs). Despite availability of effective methods for prevention, early diagnosis and treatment [2–7], women living with HIV (WLWH) have a sixfold higher risk of acquiring HPV infection and developing cancerous lesions [8], even at younger ages [9, 10].

The World Health Organization (WHO) is leading a global effort to eliminate CC as a public health problem, proposing the “90–70-90” targets to meet by 2030: 90% of girls fully vaccinated against HPV by 15 years of age; 70% of women screened using a high-performance test by 35 years of age and again by 45 years of age; 90% of women identified with CC treated and given care [11].

The United Republic of Tanzania, where this study is planned, has the highest incidence of CC in East Africa, with 10,241 new cases diagnosed in 2020, a cumulative risk of 25.3% of new cases and 24.2% of cancer-related deaths per year according to the IARC/WHO Report [12]. Among WLWH, high-risk HPV (HR-HPV) positivity rates have been reported to be as high as 46.7% [13]. Cohorts based in Dar es Salaam, Moshi and Mwanza are currently also being investigated with regard to the distribution of different HPV genotypes [14].

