CC is preventable with HPV vaccination. Following a successful pilot project in 2014 in the Kilimanjaro region among girls aged 9 – 14 years, in 2018 the Ministry of Health (MoH) of Tanzania introduced nationwide vaccination as a school-based program for 14-year-old girls [15], reaching an estimated coverage of 78% for the first dose and 49% for the second dose by the end of 2019 [16]. Nevertheless, the limitation of vaccination is the insufficient coverage of all HR-HPV types and a large and older non-vaccinated population, necessitating ongoing secondary prevention. In 2011, the MoH of Tanzania had successfully established a nationwide screen-and-treat program using speculum-aided visual inspection with acetic acid (VIA) and cryotherapy for precancerous lesions [15]. Given the higher risk for WLWH, screening is recommended at the time of HIV diagnosis and then annually [17], optimally integrated into routine HIV care, together with screening and treatment of sexually transmitted infections (STI) and female genital schistosomiasis (GS) [18].

VIA is used to identify acetowhite lesions, which if eligible according to the WHO guidelines, are treated with cryotherapy or thermal ablation.

While VIA, as well as cryotherapy for VIA positive (VIA +) minor changes can be provided effectively at a district level, many factors, including disease perception, stigma, equipment, and personnel availability can affect the uptake [15, 17]. Moreover, previous studies in Tanzania reported up to 30% of women with documented precancerous lesions not receiving cryotherapy immediately after diagnosis, and around 80% of them subsequently being lost to follow-up [15]. Further steps in the cascade of care, in the case of larger lesions or invasive cervical cancer (ICC), are hampered by additional factors including geographic confinement of cancer clinics as well as cost of service [15, 17]. Data on the number of women not receiving loop electrical excision procedure (LEEP) although indicated and/or not referred to cancer facilities once a diagnosis has been confirmed are unavailable.

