#### Physical examination / mobile colposcopy

The first participants will undergo physical examination and VIA at baseline visit, in accordance with the national guidelines, as well as HPV-testing as detailed further, until 150 HR-HPV negatives have been examined as a control population for the diagnostic sub-study. Thereafter, only participants that report vaginal symptoms (e.g., vaginal discomfort, abnormal vaginal discharge, pelvic pain, abnormal vaginal bleeding, suspected STI or CC) and/or test positive at rLFA will undergo physical examination at baseline. Otherwise, physical examination is reserved for participants with detected HR-HPV infection, and this will take place at a second visit, due to laboratory turnaround time. Physical examination is performed as per local routine, i.e., with speculum and VIA, in accordance to WHO/IARC standard recommendations [33]. Images are recorded with the aid of a mobile colposcope (EVA system®, MobileODT Ltd, Tel Aviv-Yafo, Israel). Lesion interpretation and classification will be done as specified in Annex A. If the lesion is compatible with an STI or GS, recommendations for treatment will be provided according to National Guidelines [17]. Precancerous lesions will be treated according to severity (Fig. 1 Study Algorithm; Supplementary materials: Annex B).

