#### Follow-up

The follow-up plan is determined by the analysis results (Fig. 1). If antibodies to HPV16-L1 and/or HR-HPV DNA are detected in baseline samples, the participant will be contacted within 7–14 days by phone or, if unreachable, personally notified by a community health worker, in order to plan the physical examination at the patient’s earliest convenience (either at the next CTC appointment or at an extra visit). Independently from these results and any further treatment (LEEP or thermal ablation), participants who have antibodies to HPV16-L1 and/or HR-HPV detected at baseline will be asked to repeat cervico-vaginal swab collection for Anyplex™ II HPV28 Detection and QG-MPH after 6 months. If baseline samples are negative for HR-HPV and for antibodies to HPV16-L1, re-screening will be recommended after 12 months according to the NACP guidelines.

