### Endpoints

The primary endpoint is screening coverage, defined as the proportion of WLWH enrolled in KIULARCO screened for CC in the 12 months period after implementation of HPV testing. Participants that undergo screening and transfer out to other CTC within the study period are also included. Secondary endpoints are listed in Table 3.

**Table 3 Tab3:** Endpoints

	Endpoint
**HPV prevalence & persistence**	Proportion of participants with documented HR-HPV, LR-HPV and HPV negative at baseline
	HPV genotypes at baseline
	Proportion of participants with documented HR-HPV, LR-HPV and HPV negative at follow up (6 months after the first sample)
	HPV genotypes at follow up (6 months after the first sample)
	Rate of clearance and persistence of HPV at 6 months follow-up and factors associated with viral persistence
**Cervical lesions**	Prevalence of cervical dysplasia among the patients with HR-HPV
	Prevalence of co-infection (STI and GS)
**QG-MPH® performance**	Prevalence of HSIL/CC detected by QG-MPH® in cervical smear samples
	Diagnostic test accuracy (sensitivity, specificity, PPV, NPV) in detecting patients with CIN3 + compared to colposcopy images, HPV infection detected by Seegene Anyplex ™ II 28 and histology
**Prevo-check® performance**	Prevalence of HPV16 positive CIN2 + detected by Prevo-check®
	Diagnostic test accuracy (sensitivity, specificity, PPV, NPV) in detecting patients with HPV 16 compared to Seegene Anyplex ™ II 28
**PT Monitor® performance**	Comparison of HPV16-antibody levels in women with and without HPV16-positive CIN2 + . Calculation of test performance parameters (sensitivity, specificity, PPV, NPV) at different antibody thresholds and calculation of optimum cut-off for CIN2 + detection by ROC analysis and Youden index
	Diagnostic test accuracies (sensitivity, specificity, PPV, NPV) in detecting patients with HPV16-induced CIN2 + by PT Monitor® compared to colposcopy images, HPV infection detected by Seegene Anyplex ™ II HPV 28 Detection and histology
**Screening strategy implementation**	Acceptability of cervical self-sampling
	Acceptability of proposed implemented pathway
	Adherence to follow-up
	Rate of WLWH completing the CC screening and treatment care plan
	Prevalence of cryo/thermoablation-non-eligible lesions treated with LEEP

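### Dysplasia prevalence targets all HR-HPV-positive women, but after the run-in many get a dysplasia status only if they return, so a simple proportion is biased under either denominator

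*Protocol article*

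**What the plan says.** Table 3 (Endpoints, cervical lesions) defines the endpoint as "Prevalence of cervical dysplasia among the patients with HR-HPV". HR-HPV status comes from the self-collected swab, so it is available without an examination.

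The section on physical examination and mobile colposcopy sets out who is examined and when:

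- **Run-in.** The first participants are all examined at baseline, "until 150 HR-HPV negatives have been examined as a control population for the diagnostic sub-study".
- **After the run-in, day 0.** "Thereafter, only participants that report vaginal symptoms" or test positive on the rapid antibody test (rLFA) are examined at baseline.
- **After the run-in, everyone else.** Examination is kept for women found HR-HPV positive, and "this will take place at a second visit, due to laboratory turnaround time".

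The Follow-up section adds recall within 7–14 days by phone, or by a community health worker if the woman cannot be reached. The examination then takes place at her next clinic appointment or an extra visit. The Statistical analysis section says that prevalences of secondary endpoints are estimated with 95% confidence intervals. The article does not say how an HR-HPV-positive woman who was never examined enters this one.

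Footnote d of Table 2 limits the baseline examination to symptomatic women, which does not match the section above. The two need to be reconciled. Read literally, the footnote would enlarge the group that depends on a second visit.

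**The concern.** The denominator is known for every woman with an HPV result, while the numerator is known only for those examined. After the run-in, whether a woman is examined depends on symptoms, on HPV16-L1 antibodies or on her return. Table 1 says that elevated levels of these antibodies are associated with HPV16-induced cancer or pre-cancer. The selection therefore follows from the stated examination rule and is not just a matter of chance missing data.

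Two simple proportions are possible, and they err in opposite directions. With all HR-HPV positives as the denominator, non-returners count as lesion-free. With examined women only, the women examined on day 0 for symptoms or antibodies carry too much weight.

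The Discussion says the results should inform the Ministry of Health. The share of HR-HPV positives with dysplasia bears on how many women in an HPV-based pathway would need treatment, so an understated figure would matter.

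**Working it through.** The article gives no figure for dysplasia prevalence, so there is none to reproduce. The sample size of 1200 used below comes from the Sample size section. Its two precision statements, for the primary endpoint, do hold: 1.96·√(0.30·0.70/1200) = 2.6 points (within ±3) and 1.96·√(0.10·0.90/1200) = 1.7 points (within ±2).

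**Inputs from the article**
- N = 1200. Study status reports 1500 enrolled by the end of 2022.
- HR-HPV positivity h = 46.7%. The Background says "high-risk HPV (HR-HPV) positivity rates have been reported to be as high as 46.7" per cent, so this is an upper reported figure.
- The run-in ends at 150 examined HR-HPV negatives.

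**Inputs assumed**
- Share of later HR-HPV positives examined on day 0: s = 20% (10–40% also tried).
- Dysplasia risk of 20% in women examined on day 0 for symptoms or rLFA and 10% in the rest. True prevalence is then 0.2·20% + 0.8·10% = 12.0%.
- Non-return m = 24% or 80%. The Background reports that up to 30% of women with precancerous lesions were not treated immediately, with "around 80% of them subsequently being lost to follow-up"; 0.30·0.80 = 24%. Those figures concern treatment after diagnosis, so they are only an analogue.

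**Step 1: how many depend on returning**
- HR-HPV positives: 0.467·1200 = 560.
- Run-in size: 150/(1 − 0.467) = 281, of whom 0.467·281 = 131 are HR-HPV positive.
- HR-HPV positives after the run-in: 560 − 131 = 429 (77%). With 1500 enrolled it is 569 of 700 (81%). With N = 1200 it is 296 of 360 at h = 30% and 495 of 720 at h = 60%.
- Depending on a second visit: 429·(1 − s) = 343 at s = 20%, and 386 to 257 for s = 10% to 40%. This is a majority of the later positives whenever s is below 50%.

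**Step 2: the two simple proportions**

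Cases found are 131·12% = 15.8 in the run-in, 86·20% = 17.2 on later day-0 examinations, and 343·(1 − m)·10% among returners.

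| | m = 24% | m = 80% |
|---|---|---|
| Never examined | 82 (15%) | 275 (49%) |
| Cases found | 59.0 | 39.8 |
| Cases / all 560 | 10.5% | 7.1% |
| Error | −1.5 points | −4.9 points |
| Examined | 478 | 286 |
| Cases / examined | 12.3% | 13.9% |
| Error | +0.3 points | +1.9 points |
| Standard error, √(p(1 − p)/examined) | 1.5 points | 2.0 points |

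**Step 3: other assumptions**

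Take a true prevalence of 20%, non-return of 10–50%, s of 10–40% and a risk ratio of 1–2 for day-0 women. The all-positives proportion then runs from 13.1% to 19.3% and the examined-only proportion from 20.0% to 21.7%. The pattern is the same: the first denominator can be well off, the second only a little.

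**Step 4: does weighting repair it**

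Give returners weight 1/(1 − m) and all other examined women weight 1. The weighted case count is 15.8 + 17.2 + 34.3 = 67.2, and 67.2/560 = 12.0% at either level of loss. This holds if, among asymptomatic rLFA-negative women, return is unrelated to dysplasia given the variables used. The standard error is √(131·0.12·0.88 + 86·0.20·0.80 + 343·0.10·0.90/(1 − m))/560, which is 1.5 points at m = 24% and 2.4 points at m = 80%.

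**The case against.** The strongest reply is that this is a one-line entry in a condensed article. How unexamined women enter a secondary proportion is missing-data handling, which the full protocol or SAP may settle. A reader might infer that the plan scores non-returners as free of dysplasia, but nothing in the article says so. That result follows only if the stated denominator is applied literally. An ordinary reading is prevalence among those assessed, and there the bias is at most about one standard error in the illustration.

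A reader might also carry the 80% loss over to this study. The article does not support that. The figure concerns women already diagnosed who missed immediate treatment in earlier studies. Here the women are cohort patients on ART for at least three months, with active recall. Table 2 allows examination at any time up to six months, and HR-HPV positives are asked back for a six-month swab.

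The day-0 share and the doubled risk are assumptions. The symptoms that trigger examination also point to STI or schistosomiasis. HPV results come from batches sent every 1–2 weeks, so the run-in may overshoot and leave fewer women dependent on return. Adherence to follow-up is itself an endpoint, so loss will be visible.

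All of this limits the size of the problem. It does not remove it. Recall reduces loss and the adherence endpoint reveals it, but neither adjusts the prevalence for who was examined. Nor can QG-MPH on the self-sample stand in for the missing examination, because its accuracy is itself under study.

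**Conclusion.** The point holds as a minor one. The target population is right. What does not fit it is a simple proportion, because after the run-in the chance of being observed depends on symptoms, rLFA result and return. Over all HR-HPV positives the estimate is biased downwards, by about 1.5 points at 24% non-return and 5 points at 80% if the true prevalence is 12%. Over examined women it is biased upwards by 0.3 to 1.9 points, and only if women examined on day 0 carry higher risk. Because the article gives no non-return rate, day-0 share or risk ratio, these figures show direction and plausible scale; they do not predict the study's error.

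Two further inferences would go too far. Redefining the endpoint as examined women only would give up the population the study wants to describe. The run-in women are not clearly an unselected sample either: they are the first attenders and may include self-referrals, whom the eligibility section allows. The primary endpoint, screening coverage, is unaffected.

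**What to change.** - Keep HR-HPV-positive women as the target population, and state that unexamined women are not counted as free of dysplasia.
- Report the numbers examined and not examined by route: run-in, day 0 for symptoms or rLFA, and second visit.
- Estimate prevalence by weighting or standardising examined women to all HR-HPV positives on symptoms, rLFA result, HPV genotype and age. Give the plain examined-only proportion beside it.
- Show the prevalence in run-in HR-HPV positives (about 131 under the inputs above) as a sensitivity check, noting that these are first attenders and may include self-referrals.

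The cost is a clarified endpoint definition and one extra analysis of baseline data. The confidence interval will usually be slightly wider, and more clearly so if loss is heavy (standard error of 2.4 against 2.0 points at 80% non-return in the illustration).

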### Data collection and management

Attendance to screening and its results are routinely recorded on a card given to the patient, and on paper registries. For the purpose of this study, data are additionally recorded in an online, password-protected electronic data capture software (REDCap™). The questionnaires administered to the participants will be filled out in real time by study nurses or physicians on a tablet device, while laboratory data will be entered by the laboratory technicians as soon as they become available. Data relevant for patient care will be recorded separately in the electronic database of KIULARCO (OpenMRS v2.0.6). Participant data will be managed confidentially: pseudonymized (study ID as well as NACP ID for linkage with NACP and KIULARCO dataset) for the purpose of patient care and anonymized for scientific evaluation and further dissemination of results. At baseline, sociodemographic data, medical history, laboratory analysis results as well as knowledge, attitude and practice as regards CC and HPV vaccine will be captured. A data safety and management board is not planned. Data monitoring will be performed on a regular basis by co-investigators not involved in data collection. At the end of the project, the entire database, property of IHI and USB, will be archived for minimum period of 10 years. The study represents implementation research: HPV testing and established therapeutic interventions (thermal ablation, LEEP) are already available for routine care elsewhere in the country. The experimental diagnostic tests have a minimal impact (only capillary POC test) on clinical decisions and have been granted approval by TMDA. Adverse events will not be recorded. A Data Transfer Agreement (DTA) has been signed between IHI and respectively Charité and USB.

### Statistical analysis

For the primary endpoint, the hypothesis is that implementing a bundle of interventions comprising HPV testing on self-collected samples will improve rates of CC screening among WLWH enrolled in KIULARCO from 8 to 30%. Due to the uncertainty about the WLWH population size, this hypothesis is considered as exploratory, therefore only the precision of the proportion is estimated (screening rate), with a 95% confidence interval. The proportion of WLWH attending CC screening in the post-period will be estimated with 95% confidence interval.

For the secondary and other endpoints no hypothesis will be formulated and results will be compared in an exploratory manner. Diagnostic test accuracies (sensitivity, specificity, positive predictive value and negative predictive value) will be calculated for comparison. Accuracies will be calculated with a 95% confidence interval. Prevalence of secondary endpoints will also be estimated with 95% CI's. Diagnostic tests will be pairwise compared using McNemar test. The assessment of acceptability and feasibility will be evaluated with exploratory statistics. The agreement of raters between diagnostic interpretations will be described with kappa coefficients and polychoric correlations. All secondary parameters will be reported with descriptive statistics including minimum and maximum values, interquartile range, median, mean, SD, count, and proportion as appropriate. Comparisons between study groups will be done using Kruskall-Wallis test for metric or ordinal data and Fisher's exact test for categorical data. A *p*-value < 0.05 (two-sided) is considered as statistically significant.

All evaluations will be done with the latest version of the statistical software R.

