## Methods/design

### Study design

This is a before-and after study to evaluate the impact and feasibility of upscaling CC screening and treatment services for WLWH attending a rural referral CTC in Tanzania. The main objective is to evaluate the uptake by WLWH attending screening after implementation of HPV testing on a self-sampled cervico-vaginal smear, compared to a retrospective cohort screened by VIA. HPV testing has been implemented in a bundle with: a) a smartphone integrating a mobile colposcope (EVA system, Mobile ODT, Israel) for digital enhancement of VIA examination with cervix magnification and second look/quality control; b) thermal ablation in place of cryotherapy (thus avoiding the need for replenishing nitrogen gas cartridges); and c) LEEP.

We adopted an uncontrolled before-and-after design to compare proportion of WLWH attending screening before and after implementing mentioned interventions. A sub-study with cross-sectional design aims to explore diagnostic performance of two novel tests: the first, QuantiGene-Molecular-Profiling-Histology (QG-MPH), is based on transcriptomic biomarker analysis, while the second is a serological assay to detect antibodies against HPV16-L1 [29], either with a qualitative (Prevo-Check®) or quantitative (PT Monitor®) approach (Table 1. Supplementary material Annex A1 and A2). Further objectives are to determine the adherence to recommendations after screening, to assess the prevalence of HPV genotype-specific infection as well as other co-infections, and to assess feasibility, acceptability and costs of the new implemented screening and treatment plan.

**Table 1 Tab1:** Novel assays

Test	Name	Target	Description
Lateral Flow Assay (LFA)	PT Monitor® (Abviris GmbH, Germany)	HPV16-L1 Ab	Blood-based (serum) competitive immunoassay assessing the presence of epitope-specific antibodies against HPV16-L1. Elevated levels of these antibodies are associated with the presence of HPV16-induced cancer or pre-cancer. A quantitative readout is possible with an optical table-top reader (aLF reader by Qiagen, Germany). CE-marked IVD
Rapid Lateral Flow Assay (rLFA)	Prevo-Check® (Abviris GmbH, Germany)	HPV16-L1 Ab	Qualitative (yes/no) output of LFA (PT Monitor®) in form of rapid capillary point-of-care test with a cut-off of HPV16-L1 Ab > 1000 ng/ml. CE-IVD-marked for the detection of HPV16-induced anal and oropharyngeal cancers

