## Discussion

This implementation project represents a micro-initiative, at rural referral hospital level, to contribute to the efforts of improving CC prevention and the care cascade in Tanzania, complying with the WHO and national recommendations regarding secondary and, in part, tertiary prevention. The choice of implementing treatment procedures along with HPV testing has an ethical rationale. The decision to substitute the already in-use cryotherapy with a thermal ablation device was made after frequent reports of cryotherapy gas supply challenges, with consequently missed treatment opportunities. The introduction of a mobile digital colposcope had the purpose of allowing second-look evaluations by collaborating clinicians, for continuous education and for quality improvement. The choice of a laboratory-based HPV testing platform over the on-site available Xpert® platform was firstly due to concurrent testing needs (esp. for tuberculosis diagnostics) which would have hampered an HPV-based single-visit screen-and-treat approach only, and secondarily because the chosen platform allows for identifying more individual genotypes. The choice of a before-and-after study design has certain limitations, in that the intervention effect may be overestimated by unrecorded, concurrent factors (e.g., in this case: increased patient sensitization to CC, training of personnel, screening offered 5 days a week instead of twice weekly, and financial incentives to staff performing screening), which in this case are relevant to some extent, since the ideal comparison is the WHO’s second target (70% screened). Further, the low estimates of pre-intervention screening rates (8%) may reflect incomplete reporting or heterogeneous data sources. For the purpose of this study, a digital case report form (e-CRF) was developed which could be accessed via a tablet device or computer (also provided) and filled out in real-time. This should minimize bias in data collection. Considering that CC screening was already routinely offered to the study population and that reporting may be of suboptimal quality, recall bias cannot be ruled out for the patients who had previous diagnosis of precancerous lesions, although this should not affect the primary outcome. Cost of service is a major concern regarding the sustainability of the implementation project, which we plan to address in a future publication. Provided free of charge or after a symbolic financial contribution, CC screening and treatment with VIA / cryotherapy was financially supported by non-governmental implementing partners, including financial incentives to the screening team and an additional outreach program. Currently, diagnostic and therapeutic options are limited in peripheral health-care centers of Tanzania and different factors hinder access to CC screening and treatment programs. Implementing “near-home” options may substantially increase the participation rate as well as improve the adherence to the appropriate care plan, with rationalization of health-care center resources and improvement of quality of services.

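### The main objective is a before-and-after comparison of screening coverage, but the primary analysis gives only a post-period proportion, and the 8% baseline enters without a numerator, denominator, period or source

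*Protocol article*

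**What the plan says.** The Study design section frames the main objective as uptake of screening after the introduction of self-sampled HPV testing, "compared to a retrospective cohort screened by VIA". It continues: "We adopted an uncontrolled before-and-after design to compare proportion of WLWH attending screening before and after implementing mentioned interventions".

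The Endpoints section defines the primary endpoint in one period only: "the proportion of WLWH enrolled in KIULARCO screened for CC in the 12 months period after implementation of HPV testing".

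The Statistical analysis section hypothesises that the bundle "will improve rates of CC screening among WLWH enrolled in KIULARCO from 8 to 30" percent. It calls this exploratory because the size of the population is uncertain, "therefore only the precision of the proportion is estimated (screening rate), with a 95% confidence interval". The next sentence names which proportion: "The proportion of WLWH attending CC screening in the post-period will be estimated with 95% confidence interval".

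The Sample size section then justifies 1200 women by the precision of a single proportion, at an assumed 30% and at a pessimistic 10%.

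On the baseline figure, the Discussion says that "the low estimates of pre-intervention screening rates (8%) may reflect incomplete reporting or heterogeneous data sources". On recording, the Data collection and management section says: "Attendance to screening and its results are routinely recorded on a card given to the patient, and on paper registries". For the study, data are also entered in REDCap.

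**The concern.** The question is a contrast between two periods, and the planned primary analysis is an estimate in one of them. This is not a detail left to a fuller analysis plan. The Statistical analysis section restricts the primary analysis in so many words, and an analysis plan that added the contrast would depart from it.

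Two consequences follow. First, a reader who wants the change in coverage must set the post-period interval against the figure of 8%. That treats 8% as known without error, although the article gives no numerator, denominator, calendar period or source for it. Secondly, if screens were recorded less completely before implementation than after, part of the apparent gain could be a gain in recording, and nothing in the primary analysis would show how much.

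The reason given for the restriction does not support it. Uncertainty about the population size affects the denominator of the post-period proportion as well, and an exploratory study can still report a difference with a confidence interval.

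**Working it through.** **Inputs from the article.** Baseline 8% and target 30% (Statistical analysis); N = 1200, with ±3 points at 30% and ±2 points at 10% (Sample size); about 2500 women currently in active care (Setting).

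**Assumed inputs.** The pre-period number of women is not stated, so 1200 and 2500 per period are both shown. The completeness of pre-period records is not stated, so a range is shown. Periods are treated as independent samples unless noted.

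**1. The plan's own precision figures.** Half-width = 1.96 × √(p(1−p)/n).
- p = 0.30, n = 1200: 1.96 × √(0.21/1200) = 2.6 points, inside ±3.
- p = 0.10, n = 1200: 1.96 × √(0.09/1200) = 1.7 points, inside ±2.

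Both statements reproduce. They concern the post-period proportion alone.

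**2. The contrast at the hypothesised rates.** Half-width of the difference = 1.96 × √(p₀(1−p₀)/n + p₁(1−p₁)/n), with p₀ = 0.08 and p₁ = 0.30.
- n = 1200 per period: 1.96 × √((0.0736 + 0.21)/1200) = 3.0 points. Difference 22 points, 95% CI 19.0 to 25.0; ratio 3.75 (3.04 to 4.63).
- n = 2500 per period: 1.96 × √((0.0736 + 0.21)/2500) = 2.1 points. Difference 22 points, 95% CI 19.9 to 24.1; ratio 3.75 (3.24 to 4.34).
- The 8% alone, n = 2500: 1.96 × √(0.0736/2500) = ±1.1 points.

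If coverage really rises to about 30%, ignoring the sampling error of the baseline does little harm.

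**3. The contrast in the plan's pessimistic case**, p₁ = 0.10 against p₀ = 0.08.
- Planned one-sample interval, n = 1200: 10% ± 1.7, that is 8.3% to 11.7%. It excludes a fixed 8%.
- Two-period difference, n = 1200 per period: 2.0 ± 1.96 × √((0.0736 + 0.09)/1200) = 2.0 ± 2.3, that is -0.3 to 4.3 points. It includes zero.
- Two-period difference, n = 2500 per period: 2.0 ± 1.96 × √(0.1636/2500) = 2.0 ± 1.6, that is 0.4 to 3.6 points. It excludes zero.
- Overlap also counts. With the same 1200 women in both periods and a within-woman correlation of 0.3 (both assumed), the variance numerator falls from 0.1636 to 0.1636 − 2 × 0.3 × √(0.0736 × 0.09) = 0.1148. The interval becomes 2.0 ± 1.9, about 0.1 to 3.9.

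The conclusion therefore depends on a pre-period number and an overlap that the article does not give.

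**4. Under-recording in the pre-period.** If a fraction c of screens was captured before implementation and all were captured after, the true baseline is 8%/c.

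| Capture c (assumed) | True baseline | Gain to 30% |
|---|---|---|
| 100% | 8% | 22 points |
| 80% | 10% | 20 points |
| 60% | 13.3% | 16.7 points |
| 50% | 16% | 14 points |

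At the hypothesised rates, capture of 80% already moves the gain by 2 points, about as much as the half-width of the difference at 2500 per period. Capture of 50% moves it by 8.

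**The case against.** The best defence is that the article is open about its limits. It labels the hypothesis exploratory, says that a before-and-after design may overstate the effect, lists concurrent changes (staff training, screening on five days instead of two, financial incentives), and says the 8% may be too low. It also names the WHO target of 70% screened as the ideal comparison, and a one-sample interval is the right tool against a fixed external target. At 8% versus 30% the missing interval would hardly alter the message.

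Most of that stands, and it limits what can be said. Three stronger readings are tempting and are not supported:
- **That the 8% comes from a different data source than the post-period rate.** The article never says where the 8% comes from. REDCap entries are additional to the card and registry, and nothing says that the post-period numerator will be taken from REDCap alone. Differential recording is a possibility, not a documented fact.
- **That the only comparison left is an informal one against 8%.** The WHO target is another stated comparator.
- **That Fisher's exact test is the fallback for coverage and wrongly assumes independent groups.** That test stands in the paragraph on secondary and other endpoints and is not tied to coverage. KIULARCO is an open cohort, so some overlap of women is likely, but its extent is not given.

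What the defence does not do is supply the estimate. Disclosing that an effect may be overstated does not replace estimating it with its uncertainty, and the 70% target does not answer whether uptake changed from before to after.

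**Conclusion.** The point holds as a contradiction within the article. The Study design section asks for a before-and-after comparison; the Endpoints and Statistical analysis sections confine the primary analysis to the post-period. Followed as written, the main objective receives no effect estimate. No stated figure is numerically wrong.

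The size depends on the result. If coverage reaches about 30%, sampling error in the baseline is minor and the completeness of its recording is the larger threat. If coverage reaches only about 10%, treating 8% as a constant can change the conclusion. These statements rest on assumed pre-period numbers and assumed capture rates. A reader should not go further and conclude that part of any rise must be better recording: the authors call this possible, and the article gives no measure of it.

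**What to change.** - **Primary estimate.** Make it the post-minus-pre difference in 12-month screening coverage, with the ratio alongside, each with a 95% CI. Keep the post-period proportion with its interval for comparison with the WHO target.
- **Baseline.** Define a pre-period of the same length, and use the KIULARCO women in care in each period as denominators. State the numerator, denominator, dates and source of the 8%.
- **Common source.** Count both numerators from the same routine source where one is available.
- **Dependence.** Link records by NACP ID and use patient-clustered standard errors where women appear in both periods.
- **Sensitivity analysis.** Report the gain over a stated range of pre-period completeness. The post-period overlap between registry and REDCap can inform that range, but completeness may have changed with the training, the longer service hours and the incentives. It should be labelled a sensitivity analysis, not a correction.

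The cost is a change to the analysis text and one retrospective extraction; whether the older records allow it needs checking at the site. The reported gain may turn out smaller or less certain.
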